**Analysis::**

The normality assessment will be done using Shapiro Wilk test. Cox proportional hazard regression will be used to check the univariate and multi-variable associations of independent variables with the outcome. Both intention to treat analysis and per protocol analysis would be performed.

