### 1.3 Hypothesis

#### 1.3.1 Null Hypothesis

There is a difference in the incidence of surgical site infection in bilateral simultaneous TKR patients with wound closure by Prolene vs staple.

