#### 1.3.2 Alternative Hypothesis

There is no difference in the incidence of surgical site infection in bilateral simultaneous TKR patients with wound closure by Prolene vs staple.

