## 2. Methods

### 2.1 Study Design

This study will be conducted as an open blinded, parallel design, equivalence randomized controlled trial. The patients would be randomized to receive either of the two interventions i.e., Prolene or Staples.

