### 2.8 Sample Size

The sample size was calculated via open epi software version 3.01. The level of significance was kept at 5% with a power of 80%. The percentage of exposed (staple sutures) with outcome (surgical site infection) was 66%. The percentage of non-exposed (Prolene sutures) with outcome (surgical site infection) was 33%. The estimated risk ratio taken from a study was 2. After adding the non-response rate of 10% the final sample size came out to be 82 patients with 41 patients in each arm [3].

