### 3.2 Univariate and Multivariable Analysis

The Cox Proportional Hazard regression will be used for the univariate and multivariable analysis. Univariate analysis will be conducted, and crude risk ratios and their 95% confidence intervals will be obtained. All significant independent variables at the univariate stage will be regressed by using cox proportional hazard regression using the stepwise method in the multivariable model and the adjusted risk ratios will be obtained. Both per-protocol analysis and intention to treat analysis (ITT) would be performed.

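### Significance screening and stepwise selection do not exempt the randomised arm, so the adjusted Prolene-versus-staples ratio will usually be missing, and biased when it is present

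*Protocol article*

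**What the plan says.** Section 3.2 describes two steps. First, univariate Cox models yield crude risk ratios with 95% confidence intervals. Second, "All significant independent variables at the univariate stage will be regressed by using cox proportional hazard regression using the stepwise method", and the adjusted risk ratios are taken from the resulting model. Both intention-to-treat and per-protocol versions are planned. The Analysis paragraph of the abstract frames the work the same way: "Cox proportional hazard regression will be used to check the univariate and multi-variable associations of independent variables with the outcome".

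Neither place names the closure arm as a term that is always in the model, names covariates fixed in advance, or says whether the crude or the adjusted ratio answers the primary question.

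Section 2.1 calls the study an "equivalence randomized controlled trial". Section 1.3.2 gives as the hypothesis to be established: "There is no difference in the incidence of surgical site infection in bilateral simultaneous TKR patients with wound closure by Prolene vs staple". Section 1.3.1 makes a difference the null.

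**The concern.** The procedure is one used to look for risk factors in a cohort, applied here to a randomised comparison. In a trial, the effect of the arm is the quantity to be estimated, so whether it is reported should not depend on its own p-value.

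The entry test also points the wrong way for this design. A variable enters only if it shows a difference, while the trial hopes to show that there is none. Similar arms would usually mean no adjusted treatment estimate at all. An adjusted estimate would appear mainly when chance, or chance added to a real effect, had made the observed difference large. Adjusted ratios reported under this rule are therefore a selected set, and their nominal 95% intervals ignore the selection. The covariates beside the arm would also be chosen on the outcome data, which is fragile if infections are few.

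**Working it through.** **Inputs.** 41 per arm, 82 in total; 66% (staples) and 33% (Prolene), all from section 2.8. Anticipated infection rate 2%–7%, section 2.10.1. Section 3.2 gives no entry threshold, so 5% is assumed, the level in section 2.8 ("The level of significance was kept at 5% with a power of 80" per cent).

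**The plan's own figure.** The Kelsey formula with mean proportion (0.66 + 0.33)/2 = 0.495 gives (1.96 + 0.8416)² × 0.495 × 0.505 × 2 / 0.33² = 36.03, so 37 per arm and 74 in total. Then 74 × 1.10 = 81.4, so 82. The stated size reproduces.

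**Chance that the arm passes the screen.** For each pair of true rates, the binomial probabilities of all outcomes (a, b) at 41 per arm were summed over those with p < 0.05. The tests were the two-sided chi-square, z = (a − b)/41 ÷ √[p̄(1 − p̄) × 2/41] with p̄ = (a + b)/82, and Fisher's exact test. Both are proxies for the univariate Cox test.

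| True rates | Passes, chi-square | Passes, Fisher | Arm left out |
|---|---|---|---|
| 2% each | 0.8% | 0.01% | 99% or more |
| 4.5% each | 4.0% | 0.3% | 96–99.7% |
| 7% each | 5.7% | 1.0% | 94–99% |
| 33% each | 5.0% | 2.9% | 95–97% |
| 7% vs 3.5% | 10.2% | 1.8% | 90–98% |
| 7% vs 2% | 16.6% | 3.1% | 83–97% |
| 66% vs 33% | 88% | 83% | 12–17% |

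**Size of the estimate when the arm is kept.** At low rates the smallest significant chi-square splits are 4 vs 0, 6 vs 1, 8 vs 2, 10 vs 3 and 11 vs 4. For example, 4 vs 0 gives p̄ = 4/82 and z = 2.05, while 3 vs 0 gives z = 1.76. The observed ratios are then infinite, 6, 4, 3.3 and 2.75. With a true doubling, any arm kept at these counts shows a ratio well above 2.

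**Simulation of the Cox procedure.** Univariate screen plus backward stepwise, 400 runs per scenario, with nine pure-noise covariates (an assumed number).
- The arm was kept in 0% of runs at 2% or 7% each and at 3.5% vs 7%, in 3% at 33% each, and in 85% at 33% vs 66%.
- At 33% vs 66% the median retained hazard ratio was about 3.0. The true value is about ln(0.34)/ln(0.67) = 2.7.
- At least one noise covariate ended in the model in 12–31% of runs at low rates and 25–39% at high rates.
- Wald tests behave poorly when an arm has no events, so the zeros at low rates are partly an artefact of that test.

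**Events available.** At 2%–7%: 82 × 0.02 = 1.6 to 82 × 0.07 = 5.7. At 66% vs 33%: 41 × 0.66 + 41 × 0.33 = 40.6. With SE(log HR) ≈ 2/√events, the 95% interval runs from the estimate divided by, to the estimate multiplied by, exp(1.96 × 2/√events). That factor is about 16 with 2 events, 5 with 6 events and 1.8 with 41. With equal arms, at least one arm has no infection in 68% of trials at 2% and 10% at 7%, and an ordinary Cox hazard ratio for the arm then has no finite estimate.

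**The case against.** The strongest reply is that the treatment effect is not lost. The crude ratio for the arm, with its 95% confidence interval, is obtained before any selection, and in a randomised trial that is the unadjusted comparison. This stands. A reader might infer that the plan discards the treatment effect altogether, and section 3.2 does not support that: only the adjusted ratio is at risk. What remains is that the article does not say which of the two carries the conclusion.

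A reader might also infer that the arm is dropped precisely when equivalence is true. The figures contradict this. It is also dropped in 90–98% of trials at 7% vs 3.5% and in 12–17% at 66% vs 33%, and it is kept by chance in up to about 6% of trials with equal arms. Removal follows non-significance, not the truth of either hypothesis. For the same reason, a missing arm term could not be read as support for equivalence.

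Third, the article never says outright that the arm is screened. That is the natural reading of a rule covering all independent variables, but it is an inference. A condensed article may also leave a covariate list or a forced-in term to a fuller document. That excuses missing detail. It does not excuse a stated selection rule which, if followed, does the damage shown.

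Fourth, the claim that two to six events make even one covariate too many holds only at the 2%–7% of section 2.10.1. At the 66% and 33% of section 2.8 there would be about 41 events. The conflict between those two sections is a separate matter.

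**Conclusion.** The concern holds for the adjusted treatment effect. As written, section 3.2 would leave the adjusted Prolene-versus-staples ratio unreported in about 94% or more of trials with equal arms, at every equal rate tabulated. It would also do so in most trials with a real difference within 2%–7%. Where the arm is kept, the estimate is biased away from the null. That its interval is too narrow is a general property of intervals computed after selection and was not quantified here.

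Overfitting is severe if infections run at 2%–7%, because two to six events cannot support model selection. It is milder at the rates in section 2.8. Noise variables are still picked up there, but each coefficient rests on many more events.

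The percentages assume a 5% entry level, no exemption for the arm, 41 analysed per arm, and tests of proportions in place of the Cox test. A looser entry level would keep the arm more often but would leave its reporting conditional on its own p-value.

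**What to change.** Rewrite the paragraph in section 3.2 as follows.

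- Name the unadjusted comparison of the randomised arms, reported as an estimate with its confidence interval, as the primary analysis.
- Remove univariate screening and stepwise selection from the treatment comparison.
- In any adjusted sensitivity analysis, always keep the arm and use baseline covariates fixed in advance, their number limited by the expected events. A penalised fit is one option if events are few, but it is a preference and not a requirement.
- Label risk-factor modelling as exploratory.

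The Analysis paragraph of the abstract should follow the same wording. No data collection changes. The cost is that the risk-factor table is no longer a confirmatory result. The change ensures that the treatment estimate is always reported. It does not improve precision, which at two to six events stays poor whatever model is used.

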## 4. Ethical Considerations

### 4.1 Harms and Adverse Events

There are no anticipated harms in the study. In case of any unanticipated adverse event, the Ethical review committee (ERC) of AKUH would be informed and the recommended actions would be taken.

### 4.2 Ethical Review Committee

This protocol is exempted from Ethical review committee as it’s just a protocol. All the required approvals will be taken from the ERC, CTU and from the Musculoskeletal and sports medicine service line chief. The trial is registered at *clinicaltrials.gov* and UIN of the registry is NCT04492852.

### 4.3 Informed Consent

Informed consent will be taken form the patient to enroll him/her in the study. All the required information regarding the study will be given to the patient during the process of taking informed consent. A copy of the consent form will be provided to the patients. The patients will be explained about benefits and risks attached to the study.

## 5. Dissemination of the Study Findings

Results of the study will be disseminated to the study participants, public health, and clinical professionals. The results obtained from the trial would be disseminated to all the surgeons of service line to ensure a standard practice. The results would also be published in a reputable international journal.
